**Ethics Approval and Informed Consent**

Institutional Review Board approval of the study protocol was obtained through the university committee for biomedical research (IRB-01), #201208786. This committee has provided continuous oversight and monitoring. The research protocol was registered at ClinicalTrials.gov (NCT 01763216) on January 3, 2013 (before any participants were approached for enrollment) and was updated throughout the study. Written informed consent was obtained from all participants.

**Funding**

This study was funded by the National Institute for Nursing Research Award # NIH R01-NINR13908. Posit Science Corporation provided free copies of *Road Tour* and *Double Decision* for use by participants but had no role in the design and conduct of the study, or any manuscripts submitted for publication. Licenses for *Boatload of Crosswords* were purchased from Boatload Puzzles, LLC using NINR grant funds.

**Materials and Methods**

The *Improving Mood* study was a 5-year, two arm, parallel randomized controlled trial (RCT) that compared the speed of processing training program known as *Road Tour* to attention control using computerized crossword puzzles in assisted living (AL) and related senior living settings. Three specific aims evaluated the effect of *Road Tour* vs. attention control on: (1) cognitive processing speed; (2) reducing depressive symptoms and the risk of onset of suspected clinical depression; and, (3) depression-related comorbidities including anxiety, pain, and health-related quality of life among older adults living in AL.

***Setting recruitment and engagement***

A community-based research approach was used to engage AL settings as partners in conducting the research project. The goal was to engage up to 30 AL settings that would each recruit a minimum of 10 older adult participants to achieve the target of 300 total participants. As partners in the research, each organization identified one or more staff members who completed university-sponsored, online human subjects training and acted as onsite research assistants (RAs). These onsite RAs, called Study Liaisons, were trained to recruit, consent, and train participants to use the computer games, conduct computer-based assessments, and facilitate telephone assessments conducted by university team members. Study Liaison preparation used detailed training manuals and fidelity checks performed by the Study Coordinator to assure the integrity of study procedures at partner sites.

Adaptation: Although AL programs were plentiful, the vast majority were too small to identify 10 participants who would participate, and/or didn’t have staff resources to support the participatory study approach. Moreover, senior living leaders questioned the logic of involving only AL residents, noting that many residents on the same campus were “one service away” from being classified as “assisted” based on their age, health, and function. Others indicated that they had abandoned policies that required residents to relocate when they needed services. In turn, many older adults living in housing that was defined as “independent living” (IL) on their campus were receiving personal assistance similar to those living in housing defined as AL. As a result, older adults residing in IL apartments on senior living campuses whose AL services were also involved in the study were also invited to participate.

***Study participants***

All older adults living at partner sites were invited to enroll to maximize generalizability. Inclusion/exclusion criteria included being 60 years old or older, residing in a participating AL, speaking English (the language of *Road Tour*), and self-report having sufficient visual acuity (with glasses) to use a computer, physical ability to operate a computer keyboard and mouse, and capacity to provide informed consent. Written informed consent was obtained by Study Liaisons at each site using standard procedures that were modeled by university team members to assure both comfort with the process and fidelity to the methods.

Adaptation. We adjusted the lower boundary of our inclusion criteria to 55 years to conform to admission policies in partner settings. This adjustment allowed the Study Liaisons to avoid a sense of discrimination against slightly younger adults living in their communities, and greatly simplified their advertising and recruitment approaches.

***Experimental Design***

[figure not shown]

Eligible older adults who completed informed consent with Study Liaisons were scheduled for baseline telephone interviews conducted by university team members. All primary outcome measures were collected via telephone interviews, except for the speed of processing measure (Useful Field of View, UFOV) which was collected onsite by Study Liaisons. Randomization occurred after baseline interviews were completed. Participants were asked to complete 10 hours of training during the first 5-6 weeks, and 4 additional hours of training at 5 and 11 months for a total targeted dose of 18 hours.

**Randomization.** Participants were randomized to training groups using block randomization within sites and types of care (AL and IL) to maintain balance across treatment conditions by senior living community and residence type (AL and IL). The study statistician determined the order of assignments using a computer-generated list of random numbers using block sizes of two and four. Participant IDs and assignments were concealed in sequentially numbered opaque envelopes stored in separate bins (one for each site) kept in a locked cabinet within the Study Coordinator’s office.

***Assessment and Data Management***

Computer-assisted telephone interviews (CATI) were used to assess participant characteristics and outcome measures at baseline, and outcome measures again at post-training (6-8 weeks post-randomization), and at 26 and 52 weeks post-randomization. The speed of processing assessment was administered at the four time points by Study Liaisons using study computers at partner sites. Usage information embedded in the intervention software was sent to research investigators over the internet using secure file encryption protocols. This included the number of minutes played, number of sessions, and the percentage of completing all available exercise sets.

All data collection was monitored by the Study Coordinator. Standard procedures were used for programming CATI software, interviewer training, data entry and editing, as well as database management, updating, reconciliation, data retrieval and statistical computing, and data security and confidentiality. Codes were written so that missing and implausible values were automatically flagged in real time during the interviews for verification when entered. Onsite speed of processing assessments were saved using participant ID numbers and copied to encrypted flash drives that were mailed to the Study Coordinator. Results were printed first and then entered electronically, with the printed originals kept in secure storage. All data were stored on a secure university server that is backed up daily and uses a three-tiered authorization and strong password system to protect data.

***Instruments and Measures***

**Speed of Processing Measures (Aim 1).** Speed of processing was measured using the *Useful Field of View (UFOV)* PC mouse version. The *UFOV* is well-established, has high reliability and validity, and is the gold standard for measuring visual processing speed.^1^ It is computer administered and takes 5 to 7 minutes to complete. Three subtests, stimulus identification, divided attention, and selective attention, are each automatically scored from 17-500 miliseconds (ms) reflecting the shortest exposure time at which the participant could correctly perform each subtest 75% of the time. A composite outcome score of the three subtests ranges from 51-1500 ms, with lower scores reflecting faster speed of processing. Normative data for 2759 participants aged 65 to 94 years in the *ACTIVE* clinical trial indicates that the baseline UFOV composite scores ranged from 86 to 1500 ms, with a mean of 481.9 ms and standard deviation of 247.5 ms.^2^

**Depression Symptoms (Aim 2).** The frequency and severity of depression symptoms were assessed using two self-report scales that were used at each time point. The 12-item version of the Centers for Epidemiological Studies Depression (CESD) scale^3^ is a shorter version of the original CESD-20^4^ that has been a gold standard for screening for depression in epidemiological and public surveys, and has very high reliability and validity. The CESD-12 was used in both *ACTIVE* and *IHAMS* trials which allows comparison of depression outcomes among participants in this study and subjects in earlier studies. CESD-12 is composed of short statements scored from 0=rarely or none of time (less than 1 day per week) to 3=all of the time (5-7 days per week) for a score range of 0-36, and has a cut-off score of >9 for suspected clinical depression.^5-7^

The 9-item Patient Health Questionnaire (PHQ-9)^8^ also has very high reliability and validity, is widely used in both research and clinical settings, and performs well in telephone assessments.^9,10^ The PHQ-9 items reflect the nine DSM-5 diagnostic criteria for major depression^11^ and are rated from 0=not at all to 3=nearly every day for a total score range of 0-27. Established cut-points are: 0-4=minimal depression; 5-9=mild depression; 10-14=moderate depression; 15 or greater = severe depression. Scores >10 indicate clinically significant depression.^12^ The PHQ-9 directly assesses two hallmarks of major depression (prominent dysphoria and anhedonia) and is described in a large body of late life depression research.

**Depression-Related Health Outcomes (Aim 3).** Health-related quality of life (HRQoL), pain and anxiety measures used in the study have well-established reliability and validity and age-specific national norms for comparative purposes. HRQoL was measured using the SF-36 Health Survey^13^ at baseline and 52 months to allow direct comparison of one-year effects with *IHAMS* and *ACTIVE* studies. The shorter SF-12^14^ was used at 6-8 and 26 weeks to approximate SF-36 scores at these intermediate assessments while minimizing respondent burden. Both the SF-12 and SF-36 include the standard single item self-rated health question. Pain was assessed using the Brief Pain Inventory (BPI) that was developed for assessing cancer pain, validated for use in general populations, and is widely used.^15-17^ The BPI includes four pain severity and seven pain interference items that are rated from 0 to 10, an open-ended pain severity item that is rated 0 to 10, two open-ended questions about use of medications and treatments used to treat pain, and one question about pain relief from treatments that is rated 0 to 10. Anxiety symptoms were assessed using the 7-item Generalized Anxiety Disorder (GAD-7) scale^18^ that rates the DSM-IV^19^ criteria for GAD on a scale from 0=not at all to 3=nearly every day. Cut-points for the GAD-7 are comparable to the PHQ-9, with 0-4= minimal anxiety; 5-9=mild anxiety; and >10=clinically significant anxiety.

**Covariates.** Personal and health-related characteristics were collected at baseline. Personal characteristics included: sociodemographics (age, race, sex, marital status, education, and income), social support (5 items scored on a 5-point scale from 0=none to 4=all of the time), and presence of common chronic conditions like high blood pressure, arthritis, heart disease, diabetes, lung disease, as well as anxiety disorder, depression and current use of depression treatments. Characteristics of partner organizations included number of older adults served, type of programs and services provided, type and number of staff employed, profit/ownership status, and years in operation.

***Intervention and Attention Control Training Programs***

**Intervention.** *Road Tour* is the second-generation speed of processing training program that was evaluated in *ACTIVE* (in its MS-DOS format) and used in *IHAMS* (in its MS Windows format). The training was designed to improve the efficiency and accuracy of visual information processing and the ability to perform complex visual attention tasks. It focuses on improving the speed and accuracy with which users identify and locate visual information using a divided attention format. Over time, the difficulty and complexity of each task is systematically increased as users attain specified performance criteria. Difficulty is increased by reducing visual stimuli duration, adding visual distracters, increasing similarity between target and distracter stimuli, and presenting visual targets over a broader spatial expanse.

To initiate training, the user clicks on the start button. One of two vehicles, either a car or a truck, appears in the center of screen. Seven distracter stimuli (rabbit crossing signs) and the target sign (Route 66) appear in the periphery. The stimuli (car vs. truck, and rabbit crossing vs. Route 66 sign) are presented for a specified time and then disappear briefly. A car and truck appear, and the user clicks on the correct target vehicle (car or truck). Then the user selects the circular location where the Route 66 sign had appeared. The training program is tailored to the participant’s performance by maintaining a 75% success rate before increasing the challenge level. As the user progresses, three changes increase the task difficulty: the visual field expands; an increasing number of distracters appear; and the vehicle pairs morph to become more similar and thus more difficult to differentiate.

Adaptation. Posit Science Corporation’s CD-ROM based *Road Tour* training program was used until support was unexpectedly discontinued in August 2014, roughly 17 months after starting enrollment. The web-based replacement, *Double Decision*, (<https://www.brainhq.com/why-brainhq/about-the-brainhq-exercises/attention/double-decison>) was used from 2014 through the end of enrollment in 2015. The training features of *Double Decision* are the same as *Road Tour* (as described above). The transition to *Double Decision* presented short-term delays as we developed new recruitment and training materials for *Double Decision* and negotiated support for participants already using *Road Tour* to assure use of one format or the other, but not both by a single participant.

**Attention Control.** *Boatload of Crosswords* (<http://www./boatloadpuzzles.com>) served as the attention control condition. *Boatload of Crosswords* is one of the oldest and most popular crossword puzzle games commercially available. The software offers the user a choice between three puzzle sizes, three levels of complexity, and varying font sizes. *Boatload of Crosswords* also provides optional help features, like filling in letters and words, showing incorrect letters or words in red, and solving the puzzle, that minimize frustration levels often associated with puzzle completion. *Boatload of Crosswords* was chosen for this study because, like *Road Tour*, it is computerized, very popular and easy to use; many older adults enjoy doing crossword puzzles; and it was successfully used as the attention control condition in *IHAMS*.^6^

***Approach***

The community-based approach first engaged senior living programs and services who agreed to (a) having a dedicated a staff member act as the on-site RA (Study Liaison), and (b) recruit a minimum of 10 older adults in their setting to participate in the study. Required documents for subawards were completed, signed and filed with the University Department of Sponsored Programs. Staff member(s) identified as Study Liaisons were trained and certified onsite by the Study Coordinator or her designee using university-endorsed Certifications in Human Subjects Protections (CITI) training program (<https://hso.research.uiowa.edu/certifications-human-subjects-protections-citi>). Each partner was provided two (or more) computers that were programmed specifically for study use, including fields for participants to log-on and use their assigned software, and also administration of the UFOV by Study Liaisons. The Study Coordinator and/or designated university research assistants trained Study Liaisons to (a) use *Road Tour/Double Decision* and *Boatload of Crosswords* software using detailed program materials developed for use in the study; and (b) conduct informed consent with participant, including pre-screening for inclusion criteria and capacity to sign meaningful informed consent. An individualized manual was developed for each partner that outlined (a) key contacts in the partner organization and the university research team; (b) standard procedures for study implementation, including informed consent, telephone interview methods and timing, secure storage of informed consents and UVOF data until picked up by the university research team, and management of questions by participants; and (c) suicide management protocols (given that the PHQ-9 contained a self-harm question). Study Liaison were provided practice time related to software use, and supported by university team members when conducting informed consent with their first three (minimum) participants, when providing *Road Tour* and *Puzzles* training to their first 3-4 participants (assuring support and assistance for each of the two program and sufficient repetition to be comfortable), and when administering the on-site computerized UFOV test.

Computer-assisted-telephone-interviews (CATI) at baseline post-training, 26 weeks ad 52 weeks were scheduled and monitored by the Study Coordinator, and were conducted by specially training university research team members (RAs). Telephone interviews were scheduled to fit the personal preferences and routines of individual participants. Each interview began by rechecking for comfort related to the time of day and any unexpected demands. Potential for fatigue related to the length of the interviews (30 to 35 minutes each) was be monitored by the interviewer. Warning signs of fatigue, such as audible yawning or inattentiveness, served as cues to ask the participant if he/she would like to take a short break, or suspend the interview and resume it later on. Supportive materials to advance successful completion of interviews included use of appointment cards for participants, reminders by Study Liaisons, Answer Guides that helped participants follow answer choices by scale, and partners-specific procedures for missed calls to assure smooth and timely data collection. CATI data was entered using the university-supported Research Electronic Data Capture (REDCap) management system (<https://its.uiowa.edu/redcap>). The data entry process was coded so that all items offered “pass” options and all items in one sections must be completed before moving to the next.

The CATI system operated from the highly secure College of Public Health main, multi-RAID SQL relational database server. This SQL server uses a three-tiered security system to restrict access and protect data. These steps require (1) ITS-issued and approved ID logins, (2) a strong, quarterly-changing 15-character password in conjunction with prior access authorization for the specific SQL server directories in question, and (c) specified prior approvals for read, write, and other privileges. The SQL server is automatically backed-up every night to a second multi-RAID SQL server. All SQL servers are staffed, maintained, and monitored by ITS staff 24/7.

***Analysis***

Descriptive statistics including Student’s t-tests and chi-squared analysis are used to compare the intervention and attention control groups at baseline, and to examine differences based on living setting (AL vs. IL). The original analysis plan was to evaluate the three specific aims using each person serving as his/her own control in linear panel analyses ^20^ with GEE to correct for clustering within sites, and, logistic regression GEE models for binary outcomes. Power estimates were based on the results from the earlier *IHAMS* and *ACTIVE* studies. Setting a one-tailed *α* at 0.05 and allowing for 10% attrition, we estimated > 80% power to detect the improvements in *UFOV*, 73% power to detect changes in depressive symptoms and 68% power to detect suspected onset of clinical depression.

Adaptations. Because of the inclusion of participants from IL settings, the analytic approach will be altered. We will use random effects general linear mixed models. The dependent variable will be the outcome of interest at the time point of interest. The clustering (random effects) variable will be the AL or IL from each participating senior living community. The two main factors will be intervention vs. attention control and AL vs. IL. The interaction between these two factors will be included to test for heterogeneity of treatment effects (HTEs) between AL vs. IL. Covariates will include the outcome of interest at baseline, age, and sex.

Two *ad hoc* analyses for the first specific aim will also be conducted. The first will involve expanding the intervention vs. attention control from a binary indicator to a trichotomous indicator of *Road Tour* vs. *Double Decision* vs. attention control to test for potential HTEs between the two speed of processing platforms. The second will involve opportunistic dosing testing based on whether the intervention participants completed eight or more hours of intervention training vs. less than eight hours.

References

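### Assisted-living and independent-living residents are compared with t and chi-squared tests that ignore the clustering the plan itself defines, so the p-values for that comparison are not valid under the plan's own model

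*Protocol*

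**What the plan says.** The Protocol's Analysis section opens with two uses of the same unadjusted tests: "Descriptive statistics including Student’s t-tests and chi-squared analysis are used to compare the intervention and attention control groups at baseline, and to examine differences". The first use is the comparison of randomised arms. The second is "to examine differences based on living setting (AL vs. IL"). No cluster correction is named for either.

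Clustering is recognised for the outcome models in the same section. The original plan fitted its models "with GEE to correct for clustering within sites". The adapted plan uses mixed models and states: "The clustering (random effects) variable will be the AL or IL from each participating senior living community". Those models include arm, AL/IL and their interaction.

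On size and structure, the section on setting recruitment says: "The goal was to engage up to 30 AL settings that would each recruit a minimum of 10 older adult participants", in order "to achieve the target of 300 total participants". Its adaptation paragraph adds IL residents from campuses whose AL services were also in the study. Under Randomization, participants are allocated in blocks within site and type of care.

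**The concern.** Student's t and chi-squared tests derive their null distribution from independent participants. For AL against IL, that null amounts to no average difference between the settings and no variation between units. AL/IL status does not vary within a unit, so any correlation among residents of one unit adds directly to the variance of the AL–IL difference. The unadjusted tests leave that variance out. Ordinary variation between units in income, education, health or mood can then appear as a significant AL–IL difference when the settings do not differ on average.

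What is at stake is limited to statements that AL and IL residents do or do not differ on the characteristics tested.

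**Working it through.** **No figure to reproduce.** The Protocol gives no ICC, unit size, number of IL units or significance level for these tests. Its one-tailed 0.05 belongs to the power estimates. The ICC (0.02–0.10), the unit size, the shared fraction and the two-sided 5% level below are assumptions.

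**Unit size.** The Protocol's targets give 300 / 30 = 10 participants per setting. The minimum of 10 is per setting, not per AL or IL unit. A campus that contributes both types evenly would average 5 per unit. Fifteen campuses with 10 AL and 10 IL residents each would also make 300. Units of 5 and 10 are therefore both shown.

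**Formula.** With m residents per unit, total between-unit ICC, and a part ICC_shared common to the AL and IL units of one campus (balanced campuses), the design effect (DE) is approximately

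DE = 1 + (m − 1) × ICC − m × ICC_shared

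and the actual error of a nominal two-sided 5% test is 2 × (1 − Φ(1.960 / √DE)).

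Examples with m = 10 and ICC = 0.10:
- No sharing: DE = 1 + 0.90 = 1.90, error 15.5%.
- Half shared: DE = 1 + 0.90 − 0.50 = 1.40, error 9.8%.
- Fully shared: DE = 1 + 0.90 − 1.00 = 0.90, error 3.9%.

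**Results.** Formula first, then simulated t-tests in brackets (4,000 replicates, 300 participants, no true AL–IL difference):

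| Unit size, sharing | ICC 0.02 | ICC 0.05 | ICC 0.10 |
|---|---|---|---|
| 5, none | 5.9% (6.2%) | 7.4% (7.2%) | 9.8% (10.2%) |
| 5, half | 5.3% (5.6%) | 5.9% (5.5%) | 6.8% (6.9%) |
| 5, full | 4.8% (4.9%) | 4.4% (4.1%) | 3.9% (4.3%) |
| 10, none | 7.1% (7.0%) | 10.4% (10.5%) | 15.5% (16.1%) |
| 10, half | 5.9% (5.8%) | 7.4% (7.4%) | 9.8% (9.8%) |
| 10, full | 4.8% (4.7%) | 4.4% (4.3%) | 3.9% (4.2%) |

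**When the error doubles.** An actual error of 10% needs DE ≥ (1.960 / 1.645)² = 1.42. With no sharing, that is ICC ≥ 0.42 / 4 = 0.105 for units of 5 and 0.42 / 9 = 0.047 for units of 10. With half shared and units of 10, DE = 1 + 4 × ICC, so it again needs ICC ≥ 0.105.

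**Variations, by simulation.**
- Unbalanced campuses: 20 AL and 10 IL units of 10, with only 10 campuses contributing both. Even with full sharing, the error is 5.7%, 6.6% and 7.6% at ICC 0.02, 0.05 and 0.10.
- Binary characteristic with 20% prevalence, units of 10, no sharing: 8.1% and 10.2% at latent ICC 0.05 and 0.10.

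**Arm comparison.** With arms balanced within units, the unadjusted t-test rejects in 5.1% of trials at ICC 0 and in 4.3%, 3.5% and 3.4% at ICC 0.05, 0.10 and 0.15. Clustering does not inflate it.

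**The case against.** The strongest objection concerns size. IL participants came from campuses whose AL also took part, so much of what makes one community differ from another is common to both groups and largely cancels from the AL–IL difference. A reader might infer that these tests reject at two or more times the nominal 5%. The Protocol does not support that as a general statement. It requires little sharing together with units of about 10 or more or a fairly high ICC, and none of these quantities is given. This part of the objection stands. It does not remove the problem: the plan's own random effect is the AL or IL unit, which does not assume full sharing, and campuses with AL only weaken the cancellation.

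The second objection concerns role. A reader might take these tests as the plan's check on the reason for adding IL residents, since the Protocol reports that "many older adults living in housing that was defined as “independent living” (IL) on their campus were receiving personal assistance similar to those living in" AL housing, or as the guide to reading pooled results against aims stated for AL. Neither is supported. The tests are labelled descriptive, no decision hangs on them, and IL residents were invited for recruitment and operational reasons. Whether the treatment effect differs by setting is tested by the arm-by-setting interaction in the mixed models, which carry the unit random effect. This objection also stands. Even so, the descriptive label does not make a p-value correct when its standard error omits a known source of variance.

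Finally, nothing shows that false AL–IL differences will be reported; the calculation shows only a raised chance under stated assumptions.

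**Conclusion.** The point holds as a minor defect in a stated method. AL against IL is tested as if participants were independent, although AL/IL is constant within the clusters the same section defines, so those standard errors and p-values are not valid under the plan's own model.

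The inflation ranges from none (full sharing, balanced campuses, where the test can be slightly conservative) to about 16% (units of 10, ICC 0.10, no sharing), all under the assumptions listed. Larger units, or a mix of AL and IL that varies between campuses, would raise the error for a given ICC and shared fraction.

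The consequence stops at claims about AL–IL differences. No treatment estimate depends on these tests.

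**What to change.** Either of two changes to the Analysis section resolves it:

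- Test AL against IL with the clustering structure already specified. Use a linear mixed model for continuous characteristics and a logistic mixed or GEE model for binary ones. AL/IL is the fixed factor and the community's AL or IL unit the random effect, with a community effect added where a campus contributes both. Report the AL minus IL difference with its cluster-adjusted 95% confidence interval.
- Or show AL and IL characteristics as means, standard deviations and percentages, without p-values.

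The cost is about one sentence in the plan and a few lines of code, with no new data. The first option will usually give wider intervals and fewer nominally significant AL–IL differences. The second gives up a formal test that no decision in the Protocol relies on.

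### The adapted analysis has no model that matches the Aim 2 onset endpoint: followed as written, it estimates baseline-adjusted case status rather than onset of suspected depression

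*Protocol*

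**What the plan says.** The Materials and Methods section defines Aim 2 as "reducing depressive symptoms and the risk of onset of suspected clinical depression". Under Instruments and Measures, the CESD-12 "has a cut-off score of >9 for suspected clinical depression", so the onset part of the aim is a yes/no state. The Analysis section gives onset its own power figure, 68%, at a one-tailed alpha of 0.05 with 10% attrition.

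The original plan in the Analysis section covered all three aims and included "logistic regression GEE models for binary outcomes". The Adaptations paragraph then states "Because of the inclusion of participants from IL settings, the analytic approach will be altered", followed by "We will use random effects general linear mixed models". The dependent variable is the outcome at whichever time point is being examined. The factors are arm, AL vs IL and their interaction, and the random effect is the AL or IL unit. "Covariates will include the outcome of interest at baseline, age, and sex". This is the only model class named for the three aims after the change.

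On who is in the sample, the Study participants section says "All older adults living at partner sites were invited to enroll to maximize generalizability", and no criterion listed there concerns depression. The Covariates paragraph records baseline conditions "as well as anxiety disorder, depression and current use of depression treatments", as characteristics and not as exclusions.

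**The concern.** Onset is defined only for people who do not yet have the condition. The adapted text keeps everyone, takes status at one visit and adjusts for the baseline outcome. With baseline cases included, a participant above the cut-off at follow-up may be a new case or a case that never resolved, and the treatment term does not tell the two apart.

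At stake is what the Aim 2 binary result means. A treatment that only speeds recovery in people already depressed could be reported as prevention. Conversely, a purely preventive effect would be diluted by people who cannot have an onset. The choice of a linear model for a 0/1 variable is the lesser part of the problem, because a linear model can still give a risk difference.

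**Working it through.** **1. The plan's own figure.** Inputs from the protocol: target of 300 participants, two arms, 10% attrition, one-tailed alpha 0.05, power 68% for onset. If allocation is 1:1, 300 × 0.9 / 2 = 135 per arm. The protocol gives no onset rates, baseline prevalence or effect size, only a reference to two earlier trials, so the 68% cannot be reproduced. It can only be solved backwards with the usual two-proportion formula, ignoring clustering:

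power = Φ{ [ |pC − pT| √n − 1.645 √(2 p̄(1 − p̄)) ] / √( pC(1 − pC) + pT(1 − pT) ) }

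where p̄ is the mean of pC and pT. With n = 135 per arm, 68% corresponds to control vs treated onset of 15% vs 7.0%, 20% vs 10.7%, or 25% vs 14.8%. The figure is neither confirmed nor shown to be wrong.

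**2. What onset needs, against what the adapted text provides.**
- A set of people at risk: not stated. Enrolment did not exclude existing cases.
- A model for a binary outcome: the original plan named one, the adapted text does not.
- A visit or window in which new cases are counted: the adapted text refers only to the time point of interest.

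**3. What the stated model estimates if applied to case status.** Let b be the share above the cut-off at baseline, which randomization makes equal in the two arms on average. Within an arm,

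P(case at visit) = b × persistence + (1 − b) × onset.

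There is no arm-by-baseline term, so the treatment contrast, averaged over AL and IL, estimates

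b × (difference in persistence) + (1 − b) × (difference in onset).

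**4. Two examples. All rates are assumed.**

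Example A: no effect on onset (15% in both arms), persistence 60% control vs 40% treated. At b = 20%, control is 0.2 × 60 + 0.8 × 15 = 24% and treated is 0.2 × 40 + 0.8 × 15 = 20%, a difference of 4 points. In general the difference is 20 points × b.

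Example B: no effect on persistence, onset 20% vs 10.74%, a true onset difference of 9.26 points. The difference in case status is 9.26 × (1 − b).

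| b | A: control vs treated | A: apparent benefit (true onset effect 0) | B: difference seen (true onset effect 9.26) |
|---|---|---|---|
| 10% | 19.5% vs 17.5% | 2 points | 8.3 points |
| 20% | 24.0% vs 20.0% | 4 points | 7.4 points |
| 30% | 28.5% vs 22.5% | 6 points | 6.5 points |
| 40% | 33.0% vs 25.0% | 8 points | 5.6 points |

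**5. Size of the at-risk set.** With 135 per arm, the number at risk is 135 × (1 − b): 121.5, 108, 94.5 and 81 per arm for b = 10, 20, 30 and 40%. If the stated 68% was computed on all 135 per arm, the same onset rates give power of about 64%, 60%, 55% and 50% in the at-risk set. The protocol does not say which number was used.

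**The case against.** The adapted paragraph never mentions onset or binary outcomes. Its stated reason for change is the addition of IL residents, which bears on clustering and on the AL/IL factor, not on link functions. The word general may be loose for generalized. An SAP that is not shown may retain a logistic model and define the at-risk set, and such detail is commonly left there.

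Part of this stands. It is a reading, though the natural one, that the new specification governs the onset endpoint. But the paragraph replaces a plan that expressly covered all three aims and binary outcomes, and it states a rule of its own that does not fit a named aim. That is a mismatch within the protocol and not just missing detail. Reading general as generalized does not remove it: a logistic mixed model of status at a visit, adjusted for baseline and fitted to everyone, still pools new with persisting cases.

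Two stronger readings are tempting and not supported.
- A reader might infer that the baseline covariate proves existing cases must be in the model, because case status is constant among those at risk. The baseline outcome could be the CESD-12 score, which varies among those at risk.
- A reader might infer that the stated model roughly halves the true onset effect. Take assumed rates of 20% cases at baseline, onset of 12% vs 8% per visit and 50% recovery per visit. The difference is then 5.1 points for week-52 status in everyone, 5.5 points for week-52 status among those at risk, and 9.7 points for onset at any of the three visits. Of the 4.6-point gap (9.7 − 5.1), only 0.4 (5.5 − 5.1) comes from keeping baseline cases. The rest comes from counting onset cumulatively, a definition that the protocol does not state.

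**Conclusion.** The point holds in limited form and should be fixed. The adapted analysis, followed as written for the onset part of Aim 2, estimates baseline-adjusted case status and cannot separate new cases from persistence. With no onset effect at all, it would show an apparent benefit of 2 to 8 points over baseline prevalence of 10% to 40%. That range rests on assumed onset of 15% and persistence of 60% vs 40%, since the protocol supplies no rates. The conclusion about what is estimated does not depend on those values, only on baseline cases being in the analysis.

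The documents do not establish that the sponsor decided to fit a Gaussian model to a yes/no outcome, that onset must be counted cumulatively, or that the 68% is wrong. The continuous CESD-12 and PHQ-9 analyses, the processing-speed outcome and the Aim 3 scales are not affected by this point.

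**What to change.** Add a sentence or two to the Adaptations paragraph for the onset endpoint:
- Restrict to participants with a CESD-12 score of 9 or below at baseline.
- Name when onset is counted. A single named visit or any visit through 52 weeks would both be legitimate, and the choice is the sponsor's.
- Fit a logistic (generalized) mixed model with arm, AL vs IL and their interaction, baseline CESD-12 score, age, sex and the unit random effect.
- Keep the linear mixed model for continuous scores.
- State whether the 68% power refers to the at-risk number or to all participants, and restate it if the latter.

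No new data are needed, because the CESD-12 is already collected at every assessment. The cost is a smaller analysis set for this endpoint and, if the 68% was computed on everyone, lower power than stated.
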